35^; diet (measured with validated single questions for fruit intake and vegetable intake)^36^; physical activity (measured using a validated single question)^37^; alcohol intake; smoking; weight change from baseline; self-reported adherence to anticoagulant medication; and self-reported healthcare use, including primary care visits, cardiologist visits, emergency department visits, hospitalisations (online supplemental file 7).^21^ All outcomes are measured at baseline and 3 months.

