### Randomisation and blinding

Randomisation will be conducted electronically via the REDCap software.^37^ The software will automatically allocate participants to the intervention or control group, according to the randomisation sequence generated in R (using the randomiseR package) and uploaded to REDCap, ensuring allocation concealment. The software will randomise participants based on allocation ratio with stratification by sex and site; allocation concealment will be ensured as the randomisation sequence will not be accessible to the study team. Due to the nature of the study, participants and hospital-based cardiologists, as well as research study staff involved in the recruitment, data collection and interviewing of participants will not be blinded. However, the statistician analysing results will be blinded to the allocation.

No information on intervention content will be provided to cardiologists in recruiting sites and only participants allocated to the intervention group will be able to access the intervention, as phone calls and text messages are delivered directly to their personal phone number. Although unlikely, contamination will be assessed using intervention access records and logs of communications with participants and clinicians; any contamination will be summarised overall, by intervention component and site. An exploratory Complier Average Treatment Effect analysis (described in Statistical considerations and data analysis section) will also reflect receipt of intervention components in each group. All analyses will be adjusted for site of recruitment and sex (stratification variables).

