Statistical analysis will follow trial completion and database lock and will be conducted by a statistician blinded to group allocation, guided by a predefined statistical analysis plan. Analyses will follow the intention-to-treat principle (ie, patients will be analysed within the group to which they were randomised). We will follow a published framework for intention-to-treat analysis that accounts for missing outcome data^48^: (1) attempt to follow-up all randomised participants, even if they choose to stop receiving the allocated treatment (ie, discontinued treatment), as long as they have not withdrawn from the study; (2) perform a main analysis of all observed data that are valid under a plausible assumption about the missing data; (3) perform sensitivity analyses to explore the effect of departures from the assumption made in the main analysis; (4) account for all randomised participants in the sensitivity analyses. For the primary and secondary continuous outcomes, groups will be compared at 3 months using analysis of covariance (ANCOVA), adjusted for corresponding baseline values and stratification variables. For dichotomous outcomes, groups will be compared using a log-binomial regression, while adjusting for corresponding baseline values and stratification variables as a fixed effect. Continuous variables will be reported in means and SDs, unless they are skewed in which medians and IQR will be reported, whereas categorical variables will be reported as frequencies and/or percentages. All continuous data will be checked for normality. Appropriate methods for analysing non-normally distributed data will be used where indicated. Effect estimates will be reported with 95% CIs. All statistical tests will be two-tailed, and a significance level of 0.05 will be adopted throughout. All statistical analyses will be performed using R (V.4.1.0 or higher). We will explore heterogeneity of treatment effect by sociodemographic characteristics, CHA2DS2VA (chronic heart failure, hypertension, age ≥75 years, diabetes mellitus, prior stroke, transient ischaemic attack, or arterial thromboembolism, vascular disease, and age 65–74 years) score,^4^ recency of AF diagnosis, type of AF, and recruitment setting (inpatient vs outpatient); results will be presented displaying stratification of the outcome by subgroup. An exploratory secondary analysis will estimate the the Complier Average Treatment Effect^49

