50^ to quantify the causal effect of adhering to the CHAT-AF-S intervention on the primary outcome, overall AFEQT score, provided key assumptions are met (eg, exclusion restriction; monotonicity; and Stable Unit Treatment Value Assumption). Adherence (‘treatment compliance’) will be defined a priori as meeting the minimum intervention use threshold of 4 or more outreaches completed out of 6. We will implement a two-stage least squares analysis: in the first stage, adherence (binary) will be modelled as a function of randomised assignment, and in the second stage, overall AFEQT at follow-up will be regressed on the predicted adherence from stage 1. We will also complete sensitivity analyses, defining adherence as completing 5 out of 6 outreaches and 3 out of 6 of the outreaches, as well as using a continuous adherence measure that combines outreach completion with text message engagement.

A process evaluation will be conducted following the Medical Research Council framework^51^ to assess implementation and engagement with the intervention, using intervention engagement metrics, a user experience survey, and semi-structured interviews. We will analyse engagement with the intervention using Lipschitz’s five-element standard for engagement reporting,^52^ applied to outreach completion: adherence will be defined as meeting the minimum intervention use threshold of 4 or more outreaches completed out of 6; uptake is the number of participants who complete the first outreach; frequency of use is the average number of outreaches completed per participant; and duration of use (engagement sustainment) is defined as number of participants completing the final (6th) outreach.

The MRC framework^51^ will guide exploration of how CHAT-AF-S was implemented and experienced, including engagement, acceptability (eg, satisfaction with aspects of the intervention such as content, complexity and delivery), usability, appropriateness (eg, relevance, usefulness and practicability), perceived use and contextual barriers and enablers. The Non-adoption, Abandonment, Scale-up, Spread and Sustainability framework^53^ will guide questions examining factors influencing non-adoption or abandonment and the intervention’s potential for integration into routine care, scale-up, spread and longer-term sustainability.

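### The exploratory complier analysis writes out both two-stage equations without baseline AFEQT, the covariate its parent ANCOVA uses, and so gives up precision and correspondence with the primary result

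*Protocol article*

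**What the plan says.** In the Protocol article, *Statistical considerations and data analysis*, the analysis is introduced thus: "An exploratory secondary analysis will estimate the the Complier Average Treatment Effect". It concerns the primary outcome, and adherence means completing at least 4 of the 6 outreaches. Both stages are then described. In the first, "adherence (binary) will be modelled as a function of randomised assignment"; in the second, "overall AFEQT at follow-up will be regressed on the predicted adherence from stage 1". Neither description names a covariate. Sensitivity versions move the threshold to 5 or 3 outreaches, or use a continuous adherence measure.

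Three other statements bear on the covariates:

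- The same section says the primary and secondary continuous outcomes are compared "using analysis of covariance (ANCOVA), adjusted for corresponding baseline values and stratification variables".
- *Randomisation and blinding* mentions the complier analysis and in the next sentence states: "All analyses will be adjusted for site of recruitment and sex (stratification variables". The randomisation itself is "with stratification by sex and site".
- *Outcomes* says: "All outcomes are measured at baseline and 3 months". Baseline AFEQT is therefore available.

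**The concern.** The article goes further than announcing a complier analysis: it says what is regressed on what. Elsewhere in the same section, where covariates are intended, they are listed. Sex and site reach the complier model through the general adjustment rule, but no sentence brings baseline AFEQT into it.

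Two things follow if the model is fitted as described. First, precision is lost. A complier estimate is an intention-to-treat difference divided by the adherence share, so its interval is already wider than the primary one, and the outcome variance that baseline could explain stays in. Second, the numerator is not the primary ANCOVA effect. A reader who multiplies the complier estimate by the adherence share will not recover the reported primary effect, and the gap will have nothing to do with adherence.

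**Working it through.** **Inputs from the Protocol article.** *Statistical considerations and data analysis* gives N = 480, difference 7, SD 26, two-sided alpha 0.05, power 80% and 10% dropout. Allocation is 1:1.

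**Inputs assumed.** The documents give neither the baseline to 3-month correlation r nor the share π of the intervention arm that meets the adherence threshold. I use r = 0.3, 0.5, 0.7 and 0.8, and π = 0.7 for absolute figures. I also assume no control participant receives the programme, so that the stage 1 difference equals π.

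**1. The plan's own sample size.** Per arm, n = 2 × (1.960 + 0.842)² × 26² / 7² ≈ 217, or 434 in total. Dividing by 0.90 gives 483; multiplying by 1.10 gives 478. The stated 480 reproduces. With 480 × 0.90 = 432 analysed, or 216 per arm, power is 79.9%. The SD of 26 and 216 per arm are therefore a fair basis for what follows.

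**2. Standard error of the intention-to-treat difference.**

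- Without baseline: 26 × √(2/216) = 2.50.
- With baseline: 2.50 × √(1 − r²).

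**3. Standard error of the complier effect.** With one instrument and one adherence variable, the two-stage estimate is the intention-to-treat difference divided by the stage 1 difference. Its standard error is then approximately 2.50 × √(1 − r²) / π. At π = 0.7:

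| r | √(1 − r²) | SE | 95% half-width | SE reduction |
|---|---|---|---|---|
| baseline not used | 1.000 | 3.57 | 7.0 | – |
| 0.3 | 0.954 | 3.41 | 6.7 | 5% |
| 0.5 | 0.866 | 3.10 | 6.1 | 13% |
| 0.7 | 0.714 | 2.55 | 5.0 | 29% |
| 0.8 | 0.600 | 2.14 | 4.2 | 40% |

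The last column does not depend on π, which cancels from the ratio. The absolute figures do: without baseline, the half-width runs from 9.8 at π = 0.5 to 6.1 at π = 0.8.

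**4. Simulation.** Two-stage least squares was run on 432 participants, 3,000 replicates for each r, with adherence near 70%, mildly related to baseline, and a true complier effect of 10.

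- The ratios of adjusted to unadjusted standard error were 0.96, 0.86 and 0.71 at r = 0.3, 0.5 and 0.7, in line with the formula.
- Mean estimates were 9.96, 9.83 and 9.98 without baseline, and 9.95, 9.89 and 9.99 with it (these runs also included two binary strata covariates). Neither version shows material bias.
- Adding only the two strata covariates, generated unrelated to outcome, changed the standard error by less than 1%.

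**5. Correspondence with the primary effect.** Suppose the arms differ by chance at baseline by one standard error, 2.50 points if the baseline SD is also 26. At r = 0.5 this shifts the unadjusted intention-to-treat difference by 0.5 × 2.50 = 1.25 points, and the complier estimate by 1.25 / 0.7 = 1.79 points. The primary ANCOVA removes that shift; the two-stage model without baseline keeps it. This is the same loss of precision seen in a single trial, not a further harm.

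**The case against.** The strongest objection is that this is silence, not exclusion. The article sketches the structure of two-stage least squares: the instrument, the adherence variable and the outcome. It never says the model is unadjusted. It is a condensed account that refers to a predefined statistical analysis plan, which is not shown and may list the covariates of an exploratory model. That limits the weight of the point. It does not remove it, because the article states the two regressions and no rule in it supplies baseline AFEQT. If the analysis plan does include baseline, only the published description needs to be brought into line.

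Three stronger readings are tempting, and the documents support none of them.

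- A reader might infer that sex and site are also left out. They are not: the rule covering all analyses comes directly after the complier analysis is mentioned. A general rule that a later sentence does not repeat is not a contradiction.
- A reader might infer that standard errors will come from an ordinary regression on plugged-in predictions, and so be wrong. The article names two-stage least squares and describes it in the usual way; it says nothing about how standard errors are computed.
- A reader might infer that the complier estimate is biased or in conflict with the primary analysis. Under randomisation, adjusted and unadjusted mean differences estimate the same quantity. The difference is one of efficiency and of matching numbers.

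It is also fair to object that the size depends on a correlation the documents do not give. At r = 0.3 the gain is small, so the whole range has to be shown.

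**Conclusion.** The point holds in a limited form. As written, the complier model lacks baseline AFEQT, and nothing else in the article puts it there; the stratification variables are already covered. The cost is a less precise estimate that does not correspond to the reported primary effect. The saving from adding baseline ranges from small to substantial over the correlations examined. Its direction is not in doubt for any non-zero correlation of practical size, but its amount rests on that assumed correlation. The analysis is exploratory and does not decide the trial's conclusion, so the severity is minor.

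**What to change.** State that both stages of the complier model include baseline AFEQT, together with sex and site as the general rule already requires, and that the 5-of-6, 3-of-6 and continuous-adherence versions use the same covariates. On the same participants, the reduced form is then the primary ANCOVA, and the complier estimate is the primary effect rescaled by adherence. If the analysis plan already says this, align the published description with it.

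The cost is one line of specification. The data exist, no extra collection is needed, and there is no statistical downside. The article plans database lock and analysis for mid-2026; fixing the line before then also removes a later choice between adjusted and unadjusted complier estimates.

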### Data management and monitoring

Data handling and storage will be conducted in accordance with the National Health and Medical Research Council guidelines and Australian Code for Responsible Conduct of Research. Identifiable data collected from this study will be stored on the secure research data store server provided by the University of Sydney and will only be accessible to study researchers. Questionnaire data will be collected electronically and stored on REDCap.

With participant consent, medical history data will be collected from the electronic medical record for the purpose of this study. As per the Health Records and Information Privacy Act 2002 No 71 (Schedule 1, Section 10 (1a)), the individual to whom the information relates will provide consent for use of their information, in line with the National Health and Medical Research Council’s National Statement. Data monitoring and trial audits will be conducted by an independent team with clinical trial expertise.

## Ethics and dissemination

Ethics approval was obtained from the Western Sydney Local Health District Human Ethics Research Committee (2023/ETH00765; 12 July 2023). Written informed consent will be obtained from all study participants by a research assistant before commencing any study procedures, and a copy of the signed informed consent will be provided to each participant. Participation in the study is purely voluntary, and participants may withdraw at any time without consequences. The process of communicating information to participants and seeking their consent will ensure that a mutual understanding of the research and any associated expectations are clearly understood by participants.

Study results will be disseminated in peer-reviewed publications, scientific conferences, and to professional audiences and the public. The Open Science Framework will be used for sharing study materials (eg, trial protocol and statistical analysis plan).^21^ A lay summary of the results will be prepared with our institution’s consumer group to support broader dissemination to interested community members.

Recruitment started in November 2023, and as of December 2025, a total of 481 patients were recruited (slight over-recruitment above the planned sample size of 480). Database lock and analysis are planned for mid-2026. Results from this trial will provide evidence on the impact of CHAT-AF-S programme in supporting patients with AF and improving their quality of life. The study will also provide insights into the acceptability, engagement and perceived use of AF self-management programmes. A that leverage digital technologies such as conversational AI, with potential broader applicability in other chronic conditions. If successful, this AI-supported intervention could complement usual care for patients with AF, improving engagement in self-management and health outcomes.

## Patient and public involvement

The CHAT-AF-S programme was co-designed with patients with AF, building on lessons learnt from our previous pilot trial evaluation, process evaluation and patient feedback (Australian New Zealand Clinical Trials Registry ACTRN12621000174886).^19
20
24^

Patient perspectives were embedded in the development of CHAT-AF-S through a qualitative evaluation of the pilot CHAT-AF trial, involving semi-structured interviews with 30 participants,^20^ as well as co-author lived experience. Participants valued the accessible, human-like interactions and continuity of support but emphasised the need for greater personalisation and actionable content, flexible delivery, bite-sized content delivery and control over the frequency and volume of contact. These findings informed the tailored conversational pathways of CHAT-AF-S, with options to skip or receive additional information on a given topic during a call, combining voice call and text message delivery, choice of time for the automated phone calls and additional actionable content prompting discussion with a doctor of an individualised AF action plan.
